#### 7.1.2 Safety population:

The safety population will be the set of all subjects who receive at least 1 dose of either study medication.

### 7.2 STATISTICAL ANALYSIS

#### 7.2.1 Baseline Characteristics

The demographic and baseline characteristics will be summarized. For continuous measurements such as age, the mean, median, standard deviation and range will be tabulated. For categorical measurements such as gender, the frequencies will be computed.

|                                                         |                                                 |                                                           |
|---------------------------------------------------------|-------------------------------------------------|-----------------------------------------------------------|
| Prepared by:
[name]
Date: 22.06.2010 | Approved by:
[name]
Date:22.06.2010 | Protocol No. ZYH1.09.003.01 .PROT
Version No.: 1.0 (R) |
|---------------------------------------------------------|-------------------------------------------------|-----------------------------------------------------------|

|                                                                                  |                                                                                           |              |
|----------------------------------------------------------------------------------|-------------------------------------------------------------------------------------------|--------------|
| [figure not shown] | Clinical trial Protocol for ZYH1 – Phase II
ZYH1.09.003.01.PROT

DCGI Submission | Confidential |
|----------------------------------------------------------------------------------|-------------------------------------------------------------------------------------------|--------------|

### 7.2.2 Efficacy analysis

The primary efficacy variable is the reduction in Triglyceride (TG) at Week 6 and 12 of the treatment period compared with baseline. The change from baseline will be determined as the difference between the means for the treatment period (Weeks 6 and 12) and the baseline.

For the efficacy endpoints, treatment effect will be evaluated using an analysis of variance (ANOVA) model with factors for baseline and treatment. Treatment effects will be estimated using the least-square means and 95% confidence intervals (CIs) from the ANOVA model. Statistical significance will be defined as a two-sided p-value <0.05.

All other secondary endpoints would be analysed using appropriate statistical methods.

Intent-to-treat (ITT) and/or Per Protocol (PP) analysis will be carried out for the study trial. The PP analysis will be considered definitive while the ITT analysis will be considered supportive during the trial analysis. All the subjects enrolled in the study will be considered for the safety analysis.

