**Statistical methods:**

The SAS® package (SAS® Institute Inc., USA, and Version 9.1.3) will be used for statistical evaluation.

The demographic and baseline characteristics will be summarized. For continuous measurements such as age, the mean, median, standard deviation and range will be tabulated. For categorical measurements such as gender, the frequencies will be computed.

The primary efficacy variable is the Reduction in Triglyceride (TG) at Week 6 and 12 of the treatment period compared with baseline. The change from baseline will be determined as the difference between the means for the treatment period (Week 6 and 12) and the baseline.

For the efficacy endpoints, treatment effect will be evaluated using an analysis of variance (ANOVA) model. Treatment effects will be estimated using the least-square means and 95% confidence intervals (CIs) from the ANOVA model. Statistical significance will be defined as a two-sided p-value <0.05.

|                                                         |                                                  |                                                           |
|---------------------------------------------------------|--------------------------------------------------|-----------------------------------------------------------|
| Prepared by:
[name]
Date: 22.06.2010 | Approved by:
[name]
Date: 22.06.2010 | Protocol No. ZYH1.09.003.01 .PROT
Version No.: 1.0 (R) |
|---------------------------------------------------------|--------------------------------------------------|-----------------------------------------------------------|

|                                                                                   |                                                                                                   |                     |
|-----------------------------------------------------------------------------------|---------------------------------------------------------------------------------------------------|---------------------|
| [figure not shown] | 
Clinical trial Protocol for ZYH1 – Phase II
ZYH1.09.003.01.PROT
 
DCGI Submission
 | 
Confidential
 |
|-----------------------------------------------------------------------------------|---------------------------------------------------------------------------------------------------|---------------------|

All other secondary endpoints would be analysed using appropriate statistical methods.

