### 2.2 PRIMARY ENDPOINT(S)

Percent change in TG levels from baseline to Week 6 and Week12.

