### 3. STUDY POPULATION

Subjects should be clinically diagnosed as HIV Lipodystrophy with confirmed diagnosis of HIV 1 and on highly active antiretroviral therapy (HAART) for at last 18 months with Triglyceride level ranging between 200 to 500 mg% .before getting enrolled in the trial.

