#### 3.1 NUMBER OF SUBJECTS PLANNED

The required sample size for this study to achieve 80% power at the 5% level of significance is a total of 50 subjects.

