## 5. OBSERVATIONS

### 5.1 EFFICACY

#### 5.1.1 Primary endpoint(s)

Percent change in TG levels from baseline to Week 6 and Week 12

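### The primary endpoint is declared as percent change in TG, but Section 7.2.2 and the synopsis compute an absolute difference of means, worded so that Weeks 6 and 12 may be pooled

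*Protocol*

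**What the plan says.** Two places in the protocol body define the endpoint as a relative change. Section 2.2 reads "Percent change in TG levels from baseline to Week 6 and Week12", and Section 5.1.1 repeats it as "Percent change in TG levels from baseline to Week 6 and Week 12".

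The statistics section names a primary variable without mentioning percent: "The primary efficacy variable is the reduction in Triglyceride (TG) at Week 6 and 12 of the treatment period compared with baseline". The next sentence gives the rule for computing it: "The change from baseline will be determined as the difference between the means for the treatment period (Weeks 6 and 12) and the baseline". The synopsis, under Statistical methods, has the same rule: "The change from baseline will be determined as the difference between the means for the treatment period (Week 6 and 12) and the baseline".

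Section 3 sets the entry range: "Triglyceride level ranging between 200 to 500 mg"% . The significance rule in Section 7.2.2 is "Statistical significance will be defined as a two-sided p-value <0.05". Section 7.2.3 leaves further description of the analyses to the statistical analysis plan.

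**The concern.** A percent change and a difference of means are different quantities, and the protocol presents each as the primary measure. An analyst who follows Section 7.2.2 reports mg%. One who follows Sections 2.2 and 5.1.1 reports percent.

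The trial is single-arm and open-label, so the change from baseline is the whole efficacy result. With two definitions in force, either could be presented as the primary result after the data are known.

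The time point is also unclear. A mean for the treatment period, with Weeks 6 and 12 in brackets, reads most naturally as one average over both visits. The endpoint sections name the two visits without combining them.

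**Working it through.** **Can the sample size show which scale was meant?** Section 3.1 says "The required sample size for this study to achieve 80% power at the 5% level of significance is a total of 50 subjects". It gives no effect size, standard deviation or scale, so 50 cannot be reproduced, only inverted. By the normal approximation the standardised effect is (1.960 + 0.842)/√50 = 0.396; the exact two-sided paired t-test gives 0.404. On the percent scale that fits a mean change of 20% with an SD of about 49 points (20/0.404), or 30% with about 74. The same 0.404 could equally describe a difference in mg%. The sample size does not settle the question.

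**How the scales differ.** Let b be a subject's baseline and r the fractional change.
- Mean percent change = 100 × mean(r).
- Difference of means at the same visit = mean(b × r) = mean(b) × mean(r) + cov(b, r).

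The difference of means weights each subject's relative change by baseline. A subject at 500 mg% counts 500/200 = 2.5 times as much as one at 200. Conversely, one absolute fall has different relative sizes: -60/200 = -30% and -60/500 = -12%.

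**Can the signs differ?** Take two illustrative subjects with eligible baselines:
- 220 to 286: +66 mg%, +30%.
- 480 to 384: -96 mg%, -20%.
- Mean percent change: (30 - 20)/2 = +5%.
- Difference of means: (66 - 96)/2 = -15 mg%.

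The identity agrees: mean(b) × mean(r) = 350 × 0.05 = 17.5, the covariance is -32.5, and the sum is -15. With 50 subjects, 25 going 220 to 300 and 25 going 480 to 380, the difference of means is 340 - 350 = -10 mg% and the mean percent change is (36.4 - 20.8)/2 = +7.8%.

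**How often?** This was simulated with 50 subjects per trial and 4,000 trials per scenario. The assumptions are not from the protocol: lognormal TG, median 300 mg%, between-subject log-SD 0.4, within-subject CV 25% to 50%, observed baseline restricted to 200-500, and the same true effect at both visits.

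| True reduction | Opposite signs, same visit (scale alone) | Opposite signs, pooled difference against Week 12 percent |
|---|---|---|
| 0 to 10% | about 4-16% of trials | about 7-26% |
| 20% | about 0-9% | about 0-15% |
| 30% | under 1% | under 1% |
| 40% | 0% | 0% |

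**What pooling would add, if that is the meaning.** Assume a baseline mean of 300, a 30% fall at Week 6 (210) and a 15% fall at Week 12 (255). The pooled mean is (210 + 255)/2 = 232.5, a difference of -67.5 mg%, or -22.5% of the baseline mean. Week 12 alone is -45 mg%, or -15%.

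**The case against.** Four objections deserve an answer.

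1. *Pooling is not certain.* The sentence before the computation refers to reduction at Week 6 and 12, and the rule uses the plural for means, so a difference of means at each visit is also a fair reading. This stands: a reader might infer that the plan definitely pools, but the text supports only that it may. The percent-versus-absolute conflict remains under either reading.

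2. *The endpoint sections do not say that percent change is computed per subject.* This stands too. If percent change were taken on visit means, it would be the same-visit difference divided by the baseline mean. Its sign would always agree, and scale alone would change little beyond the units. The per-subject reading is the usual one but is inferred, and the weighting and sign results depend on it.

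3. *Sign reversal is a corner case.* A reader might infer that the two definitions are likely to contradict each other. The simulation does not support that for a sizeable effect: reversals nearly vanish at a true 30% reduction. The two-subject example shows only that reversal can occur.

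4. *The statistical analysis plan will give the detail, and this is an exploratory phase II study.* A later plan can add what the protocol leaves open. Here the protocol states two rules, and the plan could follow one only by departing from the other.

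It would also go too far to call Week 6 an interim look: the protocol names it as a primary time point.

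**Conclusion.** Wrong as written. Section 7.2.2 and the synopsis prescribe a computation that does not estimate the endpoint declared in Sections 2.2 and 5.1.1, and nothing in the protocol reconciles them. This rests on the text alone and needs no assumption.

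The numerical effect depends on how the text is read. With percent change per subject, the two scales weight subjects up to 2.5-fold differently across the entry range, so the estimate, confidence interval and p-value differ. Opposite signs are a real possibility only for null or small effects, under the simulation assumptions above. If the visits are pooled, the result also departs from either visit whenever the effect changes between Week 6 and Week 12.

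A reader might also conclude that the protocol must make Week 12 the sole primary time point or move to a geometric estimate. The contradiction does not require either.

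**What to change.** In Section 7.2.2 and in the synopsis under Statistical methods, name percent change in TG as the primary variable and replace the sentence on the difference between the means. Suggested text: *For each subject, percent change in TG will be calculated as 100 × (visit value - baseline)/baseline, separately at Week 6 and at Week 12. The mean percent change will be estimated at each visit with a 95% confidence interval. Differences in mg% will be summarised descriptively.*

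Sections 2.2 and 5.1.1 can stay as they are; adding that the change is calculated per subject would remove the remaining doubt.

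Optional refinements are to state which visit carries the primary test and to estimate the change from log ratios.

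The cost is wording in the protocol, matched in the statistical analysis plan. No visit, assay or subject is added. The change should be made before the data are seen, because a choice between the two definitions made afterwards would not be credible.

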### 7.2.3 Safety Analysis

For safety analysis the frequency tabulations of abnormal physical examination and abnormal clinical laboratory findings ( $\geq 5$  UNL) will be presented for each treatment group. Summary statistics for clinical laboratory findings and vital signs will be presented. A list of concomitant medications taken during the study period will be summarised.

All adverse events seen during the study period will be listed.

All statistical analyses will be further described in the Statistical Analysis Plan.

|                                                         |                                                 |                                                           |
|---------------------------------------------------------|-------------------------------------------------|-----------------------------------------------------------|
| Prepared by:
[name]
Date: 22.06.2010 | Approved by:
[name]
Date:22.06.2010 | Protocol No. ZYH1.09.003.01 .PROT
Version No.: 1.0 (R) |
|---------------------------------------------------------|-------------------------------------------------|-----------------------------------------------------------|

|                                                                                  |                                                                                           |              |
|----------------------------------------------------------------------------------|-------------------------------------------------------------------------------------------|--------------|
| [figure not shown] | Clinical trial Protocol for ZYH1 – Phase II
ZYH1.09.003.01.PROT

DCGI Submission | Confidential |
|----------------------------------------------------------------------------------|-------------------------------------------------------------------------------------------|--------------|

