Intent-to-treat (ITT) and/or Per Protocol (PP) analysis will be carried out for the study trial. The PP analysis will be considered definitive while the ITT analysis will be considered supportive during the trial analysis. All the subjects enrolled in the study will be considered for the safety analysis.

For safety analysis the frequency tabulations of abnormal physical examination and abnormal clinical laboratory findings ( $\geq 5$  UNL) will be presented for each treatment group. Summary statistics for clinical laboratory findings and vital signs will be presented. A list of concomitant medications taken during the study period will be summarised.

All adverse events seen during the study period will be listed.

All statistical analyses will be further described in the Statistical Analysis Plan.

|                                                                  |                                                           |                                                                   |
|------------------------------------------------------------------|-----------------------------------------------------------|-------------------------------------------------------------------|
| 
Prepared by:
[name]
Date: 22.06.2010
 | 
Approved by:
[name]
Date: 22.06.2010
 | 
Protocol No. ZYH1.09.003.01 .PROT
Version No.: 1.0 (R)
 |
|------------------------------------------------------------------|-----------------------------------------------------------|-------------------------------------------------------------------|

|                                                                                   |                                                                                           |              |
|-----------------------------------------------------------------------------------|-------------------------------------------------------------------------------------------|--------------|
| [figure not shown] | Clinical trial Protocol for ZYH1 – Phase II
ZYH1.09.003.01.PROT

DCGI Submission | Confidential |
|-----------------------------------------------------------------------------------|-------------------------------------------------------------------------------------------|--------------|

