##### Exclusion Criteria(s):

- Subjects on insulin and/or glitazone / glitazar therapy
- Pregnancy and lactation
- Subjects with history of gall stone.

|                                                         |                                                 |                                                           |
|---------------------------------------------------------|-------------------------------------------------|-----------------------------------------------------------|
| Prepared by:
[name]
Date: 22.06.2010 | Approved by:
[name]
Date:22.06.2010 | Protocol No. ZYH1.09.003.01 .PROT
Version No.: 1.0 (R) |
|---------------------------------------------------------|-------------------------------------------------|-----------------------------------------------------------|

|                                                                                  |                                                                                           |              |
|----------------------------------------------------------------------------------|-------------------------------------------------------------------------------------------|--------------|
| [figure not shown] | Clinical trial Protocol for ZYH1 – Phase II
ZYH1.09.003.01.PROT

DCGI Submission | Confidential |
|----------------------------------------------------------------------------------|-------------------------------------------------------------------------------------------|--------------|

- Subjects with history of Cardiac failure.
- Subject with history of alcohol and/or drug abuse
- History of allergy, sensitivity or intolerance to the study drugs and their formulation ingredients.
- Active Opportunistic infection in last three months.
- History of malignancy or active neoplasm.
- Any active hormonal disease and/or hormonal treatment that may affect the outcomes of interest such as clinically overt hypo/hyperthyroidism, hypogonadism, hypercortisolism, or treatment with steroids or growth hormone.
- Hemoglobin below 9 g/dl or Total leucocyte count below 1000/mm^3 or Platelet count below 50,000/mm^3
- Subjects with history of myopathies or evidence of active muscle diseases or CPK ≥10 times UNL
- Subjects with history of active liver disease or hepatic dysfunction demonstrated by aspartate aminotransferase (AST) and alanine aminotransferase (ALT) ≥2.5 times of upper limits of normal or Bilirubin more than 2 times UNL

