- Renal dysfunction (serum creatinine > 2 mg%)
- Participation in any other clinical trial in past 3 months

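### The laboratory frequency tables use one upper-sided criterion (≥5 UNL) for the whole safety panel, so they cannot count low blood counts and they miss liver and kidney values beyond the protocol's own entry limits

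*Protocol*

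**What the plan says.** The safety analysis is set out in Protocol section 7.2.3, which plans "frequency tabulations of abnormal physical examination and abnormal clinical laboratory findings", and, in the same terms, under the synopsis heading on statistical methods. The synopsis text begins "For safety analysis the frequency tabulations of abnormal physical examination and abnormal clinical laboratory findings". In section 7.2.3 the criterion is attached directly to the laboratory findings: "abnormal clinical laboratory findings ( $\geq 5$ UNL) will be presented for each treatment group". No analyte is exempted, and no lower limit, grade or shift table is given.

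Two other outputs bear on laboratory safety. One is descriptive: "Summary statistics for clinical laboratory findings and vital signs will be presented". The other is a listing of adverse events. Section 7.2.3 closes by leaving further description to the statistical analysis plan.

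Section 5.2 defines the panel: complete blood count, AST, ALT, ALP, total bilirubin, GGT, serum proteins, BUN, creatinine and CPK. Table 1 schedules blood count, liver, renal and CPK tests at all four visits.

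Section 3.2 gives the levels that keep a subject out. They include "Hemoglobin below 9 g/dl or Total leucocyte count below" 1000/mm3 or platelets below 50,000/mm3, AST and ALT at 2.5 times the upper limit or more, "Bilirubin more than 2 times UNL", creatinine above 2 mg%, and CPK at 10 times UNL or more.

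**The concern.** One multiple of the upper limit is applied to analytes whose abnormalities run in different directions and on different scales. For the blood count the abnormalities that the protocol itself names in section 3.2 are low values, and the criterion looks only upwards. For liver and kidney tests it sits well above the levels that the protocol treats as disqualifying at entry.

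Safety is half of the primary objective (section 2.1). In an open-label, single-arm study of 50 subjects, the number of subjects who cross a laboratory limit is one of the few safety results that can be read directly. If the stated rule is followed exactly, the frequency table can be empty for hemoglobin, leucocytes and platelets whatever happens on treatment, and a reader could take that as reassurance.

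**Working it through.** There is no computed figure in the protocol to reproduce here. The check compares the tabulation threshold with each entry limit, for direction and for level.

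**Inputs from the Protocol**
- Tabulation threshold: ≥5 UNL, all analytes (section 7.2.3; synopsis, statistical methods).
- Entry limits (section 3.2): AST/ALT excluded at ≥2.5 × UNL; bilirubin at >2 × UNL; creatinine at >2 mg%; CPK at ≥10 × UNL; hemoglobin <9 g/dl; leucocytes <1000/mm3; platelets <50,000/mm3.

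**Assumptions (not in the Protocol)**
- ≥5 UNL means five times the upper limit. The word for times is absent in section 7.2.3, but section 3.2 expresses its limits as multiples of UNL.
- Upper limits of normal: creatinine 1.0 to 1.4 mg%; hemoglobin 15 to 17.5 g/dl; leucocytes 10,000 to 11,000/mm3; platelets 400,000 to 450,000/mm3.

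**Step 1. Direction.** Threshold = 5 × UNL.
- Hemoglobin: 5 × 15 = 75 to 5 × 17.5 = 87.5 g/dl, which is not attainable.
- Leucocytes: 5 × 10,000 = 50,000 to 5 × 11,000 = 55,000/mm3.
- Platelets: 5 × 400,000 = 2,000,000 to 5 × 450,000 = 2,250,000/mm3.

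A subject whose hemoglobin falls below 9 g/dl, or whose counts fall below the other two limits, contributes zero to the table. This conclusion does not depend on the assumed upper limits, because a low value cannot exceed a multiple of any upper limit.

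**Step 2. Level.** Ratio = tabulation threshold / entry limit.

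| Analyte | Entry limit | Threshold | Ratio | Beyond entry limit but uncounted |
|---|---|---|---|---|
| AST/ALT | 2.5 × UNL | 5 × UNL | 5/2.5 = 2.0 | 2.5 to <5 × UNL |
| Bilirubin | 2 × UNL | 5 × UNL | 5/2 = 2.5 | >2 to <5 × UNL |
| Creatinine, UNL 1.0 | 2 mg% | 5 × 1.0 = 5.0 mg% | 5.0/2 = 2.5 | >2 to <5.0 mg% |
| Creatinine, UNL 1.2 | 2 mg% | 5 × 1.2 = 6.0 mg% | 6.0/2 = 3.0 | >2 to <6.0 mg% |
| Creatinine, UNL 1.4 | 2 mg% | 5 × 1.4 = 7.0 mg% | 7.0/2 = 3.5 | >2 to <7.0 mg% |
| CPK | 10 × UNL | 5 × UNL | 5/10 = 0.5 | none |

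As an example, a subject with ALT and bilirubin both at 4.9 times UNL on treatment appears in no cell of the frequency table.

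**Step 3. CPK.** The threshold lies below the entry limit, so nothing beyond that limit is missed. The problem is a different one: a subject may enter at 5 to just under 10 times UNL and meet the criterion with no change on treatment. Whether such a subject is counted depends on how the table handles baseline, which the Protocol does not say.

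**Step 4. Other outputs.** Low and moderately high values enter the summary statistics. They also enter the adverse event listing if the investigator reports them as events. Neither output states how many subjects crossed a limit.

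**The case against.** The strongest reply has four parts.

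*The values are not lost.* This stands. A reader might infer that cytopenias would go unseen altogether, and the Protocol does not support that. They enter the summary statistics, and section 7.2.1 names the range among its baseline summaries. If the same format is used for laboratory data, a minimum would expose one severe fall and a maximum one large rise. Events may also be listed, and serious or significant ones are reported to the sponsor at once (section 8.4.2). The point is confined to the frequency tables and the missing count of subjects.

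*Entry limits are not reporting limits.* This stands in part. Eligibility and tabulation serve different purposes, and nothing requires them to match, so the high-side gap is a poor choice rather than a contradiction. Section 3.2 also joins AST and ALT with an and, so read literally an isolated rise in one of them does not exclude a subject. The direction argument for blood counts is untouched.

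*The statistical analysis plan will deal with it.* That plan may add lower-limit or graded tables, and their absence from the Protocol would be no finding. But the Protocol does not leave the criterion open. It fixes it, twice. A plan that follows it inherits the problem, and one that replaces it departs from the Protocol.

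*An empty row is not false.* This stands. A reader might take 0 of 50 as showing a rate below 1 − 0.05^(1/50) = 5.8% (one-sided 95% bound) and call that misleading. The bound is correct for a row labelled ≥5 UNL. It misleads only if the row is read as covering any abnormality, and the Protocol plans no such interval.

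Nor should the entry-limit argument be stretched to serum proteins, which have no entry limit. Only the direction argument applies to them.

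**Conclusion.** The point holds for the frequency tables. By construction, they cannot count falls in hemoglobin, leucocytes or platelets, including falls below the Protocol's own entry limits. This needs no numerical assumption beyond reading ≥5 UNL as a multiple of the upper limit. On the high side, the tables start at 2.0 times the AST/ALT entry limit, 2.5 times the bilirubin limit, and 2.5 to 3.5 times the creatinine limit. The creatinine range rests on an assumed UNL of 1.0 to 1.4 mg%. CPK is the exception and needs only to be read against baseline.

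The documents do not support the stronger conclusion that laboratory harm would be hidden from the report. What is missing is the number of subjects affected. This should be corrected because safety belongs to the primary objective and the correction is cheap. It does not threaten the efficacy analysis.

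**What to change.** In both section 7.2.3 and the synopsis, replace the single criterion with analyte-specific, two-sided tabulation:

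1. Shift tables (low, normal, high by the laboratory's reference range) from baseline to the worst post-baseline value. For analytes that matter in both directions, show the lowest and the highest value separately.
2. Counts of subjects who newly cross the Protocol's own entry limits for AST/ALT, bilirubin, creatinine, CPK, hemoglobin, leucocytes and platelets. Newly means within the limit at baseline and beyond it afterwards. State whether the AST/ALT limit applies to either enzyme or to both.
3. The ≥5 UNL count, kept as an additional row, with the word times added and baseline status shown so that CPK can be interpreted.

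These are reporting cut-offs only and imply no change to eligibility or to the management of subjects. The cost is a few more tables. The data are already collected at every visit under Table 1.
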